#### Secondary target group

Only nursing staff responsible for incontinence care of participants in the primary target group within the respective inpatient nursing facility will be recruited. In addition, they must have attended the training sessions concerning the use of the digital assistance system and must have consented to participate in the study.

### Group assignment

The aim is to ensure that IG and CG do not differ beyond the intervention with regard to the prognostic factor of the individuals' cognitive performance. Especially with a small sample size, a different approach could promote an unbalanced relationship between the two groups [31]. An independent researcher, who is not involved in the study, performs the allocation with the software Excel (version 2018) using a randomization list with simple random sampling. During this process, participants are also assigned a code (participant ID), under which they and their data are managed in the further course of the study.

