Concerning the *primary target group of care recipients*, a two-arm, stratified and randomised, controlled interventional study is selected for the study design (RCT). Participants will be assigned to the intervention group (IG, equipped with a digital assist system) and control group (CG, not equipped with a digital assist system) study arms, and the assignment of study participants to arms will be randomized. To ensure a homogeneous distribution regarding the prognostic factor of impaired abilities to the IG and CG, a simple disproportionate stratification will be performed prior to the randomisation. This will ensure that a valid interpretation on the efficacy of the intervention is possible. Other advantages of this approach refer to a reduced probability of an α and/or β error when interpreting the results, furthermore the statistical validity of the results with a comparably low participant number is increased, and interim analyses are simplified [31–33]. The participants will be stratified using the Mini Mental Status Examination (MMSE). On the basis of the points achieved in the questionnaire, care recipients will be allocated to the subgroups “cognitively impaired” (points < 18) and “not cognitively impaired” (points > 18). In previous studies, the use of self-reported scales up to an MMSE point value of > 10 proved to be appropriate [including [34, 35]. However, in the study implementation, the results of the MMSE are used for stratification from a score of > 18. As a result, the RCT is based on the original values of the instrument [36]. Participants that have been identified as cognitively impaired by the assessment results of the MMSE (score 0 to 18) will be reported back: both nursing staff and participants affected shall estimate as objectively as possible whether the benefit of self-reported scales is appropriate. Participants who score below 18 on the MMSE or for whom assessment feedback argues against self-assessment scales will be administered assessments as third-party assessment scales.. After stratification, the participants of the two subgroups will be randomized individually to the two study arms IG or CG (see Fig. 1).

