**Fig. 1 Fig1:**
[figure not shown]
Flow chart concerning the primary target group [37]

Concerning the *secondary target group of nursing staff*, a single-armed observational study design is selected. All participants will be surveyed both quantitatively and qualitatively at four time points.

When randomizing both groups, additional attention will be paid to the individual framework conditions of the participating inpatient care facilities and they will be appropriately responded to.

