### Power calculation

The sample size calculation is based on the RCT by Chittrakul et al. [51] in which a special exercise program for fall prevention to avoid falls and increase the quality of life was developed. The result of the RCT was that the participants in the IG fell on average 1.13 times (SD = 0.84) and in the CG the average was 2.22 [51]. For the current sample size calculation, a more conservative estimate was made (M = 1.65) since a less intensive intervention is to be studied that is nevertheless of high clinical relevance. To detect a significant difference between the two groups in a two-arm test with a significance level of 0.05 and 80% power, we need at least 34 persons in each group. Thus, a total of at least 68 persons will be included. Due to the high vulnerability of the sample and assuming a drop-out rate of about 15%, a total of 80 indiviudals will be included with 20 participants from each nursing facility (primary target group). The participants will be divided into an intervention group and a control group.

Concerning the nursing staff, as secondary target group, about six to eight individuals in each inpatient facility, who are responsible for the incontinence care of the participants in the primary target group and routinely use the assistance system in their daily professional practice will be recruited. The sampling of nursing staff follows a qualitative approach and aims to ensure the representativeness of the target group [38] by contrasting characteristics such as gender and professional experience.

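### MMSE stratification is said to ensure balanced arms, but the stated simple-random list has no restriction within strata, so that balance is not assured

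*Protocol article*

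**What the plan says.** Methods and design gives the purpose of stratifying: "To ensure a homogeneous distribution regarding the prognostic factor of impaired abilities to the IG and CG, a simple disproportionate stratification will be performed" before randomisation, using MMSE subgroups. It also claims a statistical gain: "Other advantages of this approach refer to a reduced probability of an α and/or β error when interpreting the results". Both that section and Recruitment say that residents in each subgroup are then randomised individually to the two arms.

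Group assignment repeats the aim, "The aim is to ensure that IG and CG do not differ beyond the intervention with regard to the prognostic factor" of cognitive performance, and gives the reason: "Especially with a small sample size, a different approach could promote an unbalanced relationship between the two groups". The same paragraph then names the mechanism: an independent researcher "performs the allocation with the software Excel (version 2018) using a randomization list with simple random sampling". Nothing in the article restricts the list within a stratum.

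On facilities, the end of Methods and design (after Fig. 1) says only that, at randomisation, "additional attention will be paid to the individual framework conditions of the participating inpatient care facilities and they will be appropriately responded to". Power calculation plans 80 residents, "with 20 participants from each nursing facility". Recruitment allows replacement of dropouts for up to two months after the start of the system test period. Blinding says that participants, nursing staff, the system provider and study staff all know the assignment.

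**The concern.** Stratification evens out the arms only if allocation inside each stratum is restricted, by blocks, a fixed quota or minimisation. If each resident is assigned by an independent even-odds draw, the stratum label has no influence on the draw, and the arms can differ on MMSE as much as if nobody had been stratified. The stated mechanism would then not serve the stated purpose. This is more than detail left to a fuller document, because the article names both the aim and the method, and the two do not fit.

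MMSE is the protocol's own prognostic factor. It also helps decide whether quality of life and sleep are self-reported or rated by a third party, so an imbalance would shift the mix of rating modes between arms. Statistical methods further plans to present results by stratum, where uneven splits inside a small stratum would show directly.

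**Working it through.** **Inputs from the protocol.** N = 80 in four facilities of 20; at least 34 per group; two MMSE strata; allocation as quoted; 5% significance level (taken as two-sided) and 80% power; means 2.22 and 1.65, SD 0.84; 15% dropout.

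**Assumption.** Stratum sizes are not given. I use 40/40, 50/30 and 60/20 (impaired/not impaired). By symmetry, swapping the labels changes nothing.

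**Step 1: the protocol's own sample size.** Reading 1.65 as the intervention mean, the difference is 2.22 − 1.65 = 0.57. Then n per group = 2 × (1.96 + 0.8416)² × 0.84² / 0.57² = 34.09. The stated 34 is reproduced, apart from rounding up. Allowing for dropout, 68 / 0.85 = 80.

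**Step 2: simple randomisation within strata equals simple randomisation without them.** In both cases each of the 80 residents goes to either arm with probability ½, independently of the others and of MMSE. The joint distribution of assignments is therefore the same.

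**Step 3: size of the imbalance.** Let n₁ and n₂ be the stratum sizes, with a ~ Bin(n₁, ½) impaired and b ~ Bin(n₂, ½) unimpaired residents in the intervention arm. The difference in share impaired is

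D = a/(a + b) − (n₁ − a)/(80 − a − b).

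Summing the exact binomial probabilities for simple randomisation within strata, and simulating 200,000 trials for the other two schemes, gives:

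| Strata | Mean abs. D, simple within strata | Mean abs. D, simple, no strata | Chance abs. D ≥ 10 points, simple within strata | Same, no strata | Same, blocks of 4 within strata |
|---|---|---|---|---|---|
| 40/40 | 9.0 points | 9.0 points | 43% | 44% | 0% |
| 50/30 | 8.8 | 8.8 | 37% | 37% | 0% |
| 60/20 | 7.8 | 7.8 | 33.5% | 33.5% | 0% |

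The 43% and 44% differ only by rounding and simulation error. A difference of 20 points or more has a chance of 9%, 7% and about 4.5% under simple randomisation within strata.

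Hand check for 40/40: the SD of D is about √(0.5 × 0.5 × (1/40 + 1/40)) = 0.112, and the mean absolute value is about 0.798 × 0.112 = 0.089, in line with 9.0 points.

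**Step 4: within a stratum.** The chance of a 60:40 or worse split is 27% in a stratum of 40, 36% in one of 30 and 50% in one of 20.

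**Step 5: blocks of 4 and 6.** An unfinished block of 6 leaves a stratum at most 3 residents out of balance. The worst case is 3 in opposite directions in the two strata. The arms are then 40:40 and the numbers impaired differ by 3, so D = 3/40 = 7.5 points, still below 10.

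**Step 6: power under unequal arms.** With standard error 0.84 × √(1/n_IG + 1/n_CG) and power Φ(0.57/SE − 1.96):
- 40:40: SE 0.188, power 86%
- 33:47: SE 0.191, power 85%
- 32:48: SE 0.192, power 84%

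**The case against.** The best counter-argument concerns the wording. Simple random sampling ordinarily means drawing a fixed number from a list without replacement, and the protocol uses other survey-sampling vocabulary when it describes the stratification. Recruitment can be read as a batch process: residents are tested, placed in strata, then randomised. Drawing exactly half of each stratum would balance MMSE almost perfectly. This reading is possible, so the arithmetic above is conditional. But no quota is written, and replacing dropouts for up to two months fits a one-time draw poorly. Either way, the text must state the restriction.

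It is also fair that the planned regression, multilevel and stratified analyses can absorb much of a chance imbalance, and that the MMSE classification keeps its other uses (choice of rating mode, stratified presentation) under any allocation method.

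A reader might infer more than the documents support:
- **That the trial risks missing its 34 per arm.** Simple randomisation puts one arm below 34 in about 15% of trials, but the protocol does not claim that stratification secures that number, and Step 6 shows that a 33:47 split costs about one point of power.
- **That uneven splits within facilities break a promise.** Balance is claimed for cognition only. Not stratifying by facility is a design choice.
- **That the facility sentence lets allocations be altered.** It is vague, but does not say so, and an independent researcher performs the allocation. Selection bias is not shown.
- **That chance imbalance is bias.** Under valid randomisation it costs precision and face validity.

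**Conclusion.** The point holds as a mismatch between stated purpose and stated mechanism. Read as simple randomisation within strata, the list leaves a chance of 33.5% to 43% of a 10-point or larger difference in the share impaired, the same as with no strata. This rests on N = 80 and on assumed stratum sizes from 60/20 to 40/40. The conclusion is that balance is not assured, rather than that the arms will be unbalanced or that stratifying has no use at all. The consequence is lost precision and a claim that cannot be defended if the arms turn out uneven; the direct loss of power is one to two points. For facilities the defect is narrower: an undefined response to local conditions at randomisation needs a stated limit.

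**What to change.** 1. **Group assignment.** Replace the simple random sampling wording with a concealed 1:1 list, prepared by the independent researcher, using randomly varying permuted blocks (for example 4 and 6) within each MMSE stratum. If the intention is to draw a fixed half of each stratum, state that and say how replacements are allocated.
2. **Statistical methods.** Adjust the primary analysis for MMSE stratum. Facility can enter as a covariate in the planned regression or multilevel analysis; stratifying by it is optional.
3. **Methods and design, sentence after Fig. 1.** State that facility conditions affect logistics only and never change an allocation.

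The cost is a different list and a few sentences, but it must be done before randomisation, since the allocation cannot be redone afterwards. There is one real downside. Because staff know the assignments, the last places in a block can sometimes be guessed, and nursing staff forward the names of interested residents. Varying the block sizes and concealing the list limit this. Very short blocks in many small cells would make it worse, which is a reason not to cross facility with MMSE by default.

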### Blinding

The study information for participants includes information about the assigned arms and the randomised design of the study. An independent researcher not involved in the study performs the allocation using Excel. Participants, nursing staff, the provider of the digital assistance system and research study staff will not be blinded to the group assignment.

### Data management

Data management is divided into two strands. First, data from all survey points, all measurement times and assessment tools (e.g., MMSE) will be documented using electronic case report forms (eCRF). If possible, a plausibility check is performed when the data is first entered into the system. Only the anonymised particpant IDs are used for the eCRFs. Identifying data that enables the allocation of a participant ID to an individual are stored separately. Only the project management has access to this data after random allocation and assignment of the participants IDs. The data is stored on a central network system based on the data management system of the Neubrandenburg University of Applied Sciences in line with current standards for data security. Access to this network system is only granted to study staff at the Neubrandenburg University of Applied Sciences. Access to the system can only be granted by the technical administrator of the Faculty of Health, Nursing, Management after prior agreement. After completion of the study, the identifying data will be stored physically separate in the Neubrandenburg University of Applied Sciences. All study information in paper format, including the written declarations of informed consent and the questionnaires, will be stored in sealed filing cabinets in areas with restricted access. The individuals included in the study provide a written declaration of informed consent based on comprehensive verbal and written information provided about the study. All consent forms will be stored in the Neubrandenburg University of Applied Sciences. If a study participant limits his or her consent, the limitation is documented and the subsequent data analysis is performed in accordance with the imposed limitations. If a person withdraws his or her consent, all data will be removed, with the exception of data that was published prior to the withdrawal of the consent. All data will be analysed only in an anonymised format. For publications, only aggregate data that does not permit personal identification will be used. Data will only be shared without identification of the participants. Data management and the documentation process will be monitored by the study management.

The second part of the data management covers data collected during the study intervention. The data transfer between the individual components of the digital assistance system (wearable, node, edge computer, cloud) is end-to-end encrypted using a high security standard. End-to-end encryption means that no plain text is transmitted at any point during data transmission and the transferred data can only be decrypted by the intended senders and recipients. The sensor data will be transferred in anonymised format by allocating it to the ID of the wearable. Personal data (name of the resident, sex, date of birth, assigned wearables, nursing facility, room information, assigned ward mobile phone/nursing staff) is also stored in a particular part of the cloud backend, the Business Logic Server, and the sensor data will be allocated to the participant’s personal data using the wearable ID. This allocation is essential because otherwise a detected incontinence event cannot be matched to a resident and the responsible nursing staff cannot be informed via digital end device. The merging of sensor data and personal data in the cloud backend meets high security standards and thus ensures that the system offers as few attack points as possible for an unauthorized extraction, manipulation or use of personal data, e.g. by hackers.

After completion of the project, the records, transcripts and questionnaires will be sealed, stored for ten years and then destroyed. The contact data necessary to carry out the study is stored separately from the records, transcripts, questionnaires and description of the results. Both data sets will be kept locked. The mandatory data protection information required by law is complied with (2016/679/EU and State Data Protection Act for the State of Mecklenburg-Vorpommern of 22.05.2018).

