#### Dropout criteria of the primary target group

Individuals may withdraw from their study participation at any time. They or their responsible nursing staff can revoke their consent to participate in writing. Likewise, they are automatically excluded from the RCT if they die during the intervention.

A deterioration in their health does not necessarily lead to exclusion from the RCT. Those affected are only excluded from further study events if the deterioration is due to compelling medical and/or nursing reasons requiring a termination of their participation in the study.

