### Endpoints

#### Endpoints of the primary target group (care recipients with urinary and faecal incontinence)

Occurring falls represent the primary endpoint of the RCT. Secondary endpoints include cognitive ability, quality of life, sleep quality and disruptions of sleep, incontinence material consumption and general health.

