### Recruitment

#### Primary target group

The recruitment procedure is divided into two phases: 1) The study staff of the Neubrandenburg University of Applied Sciences and those responsible from AssistMe will visit the participating inpatient nursing facilities. In an open event all residents of the facility who are interested will be informed about the RCT (including the aims of the study, procedure and the intervention). This is meant as opportunity to ask questions to the persons responsible for the RCT. This shall emphasise the absolute voluntary nature of study participation. 2) If the residents or their family caregivers/legal guardians indicate interest in participating in the study, they inform the responsible nursing staff in the facility. The nursing staff consolidate the interested parties and forward their names to the study staff at the Neubrandenburg University of Applied Sciences. The study staff then visits the interested parties again. In a conversation, they will be again informed in detail about the RCT as well as the intervention. In addition, the inclusion and exclusion criteria will be checked. Residents who meet the eligibility criteria and who would like to participate in the RCT are then examined regarding their cognitive performance using the Mini Mental Status Examination (MMSE). Depending on their score, they are assigned to the respective strata "cognitively impaired" or "not cognitively impaired." Subsequently, both subgroups are randomized individually into the intervention and control group.

Should individuals in the primary target group drop out of the RCT prematurely (e.g., due to compelling medical or nursing reasons), new particpipants will be recruited and included if they meet the inclusion criteria. This post-recruitment is foreseen up to a maximum of two months after the start of the system test period.

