### Data monitoring and recording

A Data Monitoring Committee (DMC) is not established as there is no blinding and adverse events can be reported directly to the study staff. All aspects of the intervention are part of the conventional nursing care of incontinence. There are no interim analyses planned and all results will be analysed after the data collection is completed.

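### Erasing all data when consent is withdrawn removes falls already recorded and prevents analysis of those residents in their randomised arm

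*Protocol article*

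**What the plan says.** The rule is in the Data management section of the protocol article: "If a person withdraws his or her consent, all data will be removed". Only results that have already appeared in print are exempt. The sentence before it allows a participant to limit consent, with the limitation documented and respected in the analysis.

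The exception for published data will rarely apply, because Data monitoring and recording says: "There are no interim analyses planned and all results will be analysed after the data collection is completed". The data at stake include the main outcome: "Occurring falls represent the primary endpoint of the RCT".

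Other sections bear on who leaves and what follows:

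- Blinding: "Participants, nursing staff, the provider of the digital assistance system and research study staff will not be blinded to the group assignment".
- Possible harms names burdens tied to the system: a sense of being monitored by continuous recording, staff worry about being checked, and extra time and technical load for staff. It also lets intervention residents return to standard care if the system causes problems.
- Dropout criteria of the primary target group, on withdrawal: "They or their responsible nursing staff can revoke their consent to participate in writing". On death: "they are automatically excluded from the RCT if they die during the intervention".
- Recruitment provides for replacing dropouts: "This post-recruitment is foreseen up to a maximum of two months after the start of the system test period".
- Power calculation allows for about 15% dropout, from 80 residents to 68.

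**The concern.** Randomisation protects the comparison only while residents can be analysed in the arm to which they were assigned. A resident who withdraws after three months may have several recorded falls, and the rule deletes them together with the baseline data that would show what kind of resident left. If withdrawal is related both to arm and to fall risk, the residents who remain are no longer comparable. Everyone knows the allocation and only one arm carries the sensor, so a difference in withdrawal between arms is plausible from the protocol's own account.

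Ordinary dropout leaves partial data that can be used with time at risk or examined in sensitivity analyses. Erasure leaves nothing to examine, so the trial could not show that its losses were harmless. Replacing dropouts restores the headcount but not the comparison. This is therefore not a detail that an analysis plan could settle later: the protocol fixes a data-handling rule that such a plan cannot undo.

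**Working it through.** **1. The plan's own figures.** Inputs from Power calculation: control mean 2.22, planning mean 1.65, SD 0.84, significance level 0.05, power 80%, 34 per group, 15% dropout, total 80. I read 1.65 as the intervention mean, so the planned difference is 2.22 − 1.65 = 0.57. Sidedness is not stated; two-sided fits best.

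- n per group = 2 × (1.960 + 0.842)² × 0.84² / 0.57² = 34.1. Rounded up this is 35, and the t-test solution is 35.1. The stated 34 agrees to within about one resident, and power with 34 per group is 79.9%.
- 68 / 0.85 = 80, as stated. The allowance is 0.15 × 80 = 12 residents, about 6 of 40 per arm if the arms are equal.

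**2. What the rule erases.** The 15% covers dropout from any cause, which would include deaths and terminations for medical reasons. The Data management rule is triggered only by withdrawal of consent. The documents do not give that share, so I vary it from 5% of one arm (2 of 40) to the full 15% (6 of 40).

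**3. Illustration of bias (assumed values).** Suppose there is no true effect and the mean is 2.22 in both arms before erasure. A share q of one arm is erased, and those residents fall at h times the rate of the others in that arm. The mean of those who remain is

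remaining mean = 2.22 / ((1 − q) + q × h)

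| Erased in one arm (q) | Erased in the other | h | Mean remaining | Spurious difference | Share of 0.57 |
|---|---|---|---|---|---|
| 5% | none | 2 | 2.22 / 1.05 = 2.114 | 0.11 lower | 19% |
| 15% | none | 2 | 2.22 / 1.15 = 1.930 | 0.29 lower | 51% |
| 15% | 7.5% | 2 | 1.930 against 2.22 / 1.075 = 2.065 | 0.135 lower | 24% |
| equal | equal | same | equal | 0 | 0% |
| 5% | none | 0.5 | 2.22 / 0.975 = 2.277 | 0.06 higher | 10% |
| 15% | none | 0.5 | 2.22 / 0.925 = 2.400 | 0.18 higher | 32% |

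Erasure unrelated to falls (h = 1) also gives zero. The value h = 0.5 only shows the reversal of sign. None of the values of h comes from the documents.

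**4. Effect on precision.** With SD 0.84 and a difference of 0.57, power is 79.9% with 34 per arm and 85.9% with 40 per arm. The second figure is an upper limit for what retention could give, since some residents would still refuse and those who leave early contribute less time. The planned total of 80 does not change.

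**The case against.** The strongest objection is that the rule matters less than it first appears. Three parts of that case stand.

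- **Routes short of erasure exist.** Consent can be limited, and an intervention resident troubled by the system can return to standard care. The protocol does not call that a withdrawal. The most obvious arm-specific reason for leaving therefore need not trigger deletion.
- **Size and direction are unknown.** Applying the whole 15% to selective erasure in one arm is an extreme case. Immobile residents are eligible, and residents who leave because they are very frail may fall less than others, which would reverse the bias.
- **Erasure is a promise to participants.** It was made under ethics approval and stated data-protection law. Whether data may be kept after withdrawal depends on consent forms that are not shown, and deletion must remain available to anyone who asks for it.

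Two stronger readings are tempting but unsupported. A reader might infer that falls of residents who die are also deleted. The text excludes them from the trial under dropout criteria, which can mean only that participation ends, and no section orders deletion after death. A reader might also infer that a nurse can cause a resident's data to be erased. The wording leaves unclear whose consent the nurse revokes, and the deletion rule speaks of a person withdrawing their own.

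None of this answers the central point. Where a resident does withdraw consent, deletion is the stated default and cannot be reversed.

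**Conclusion.** The concern holds for withdrawal of consent. The protocol makes erasure of recorded falls the default, in an unblinded trial whose analysis comes only after data collection, so residents who withdraw cannot be analysed as randomised and their loss cannot be assessed.

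Bias is possible, not shown. On the assumptions of a 2.22 mean, no true effect and a doubled fall rate among those erased, loss of 5% to 15% confined to one arm imitates 19% to 51% of the planned effect. Balanced loss gives zero and a lower fall rate among those erased gives the opposite sign. It would go too far to say that the rule will manufacture a benefit for the system, or that deaths and nurse revocations delete data. The wording on those two needs clarifying only. This should be fixed, because the loss is irreversible and the remedy is cheap.

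**What to change.** Amend Data management so that three events are recorded separately: ending use of the system, ending follow-up, and asking for deletion. At withdrawal, ask the resident or guardian whether data collected so far may be kept and whether the facility's fall records, which are mandatory in any case, may still be read. Delete only on refusal, and count and report deletions by arm. State that all randomised residents with retained data are analysed in their assigned arm, with falls and time at risk counted up to withdrawal or death.

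In the dropout criteria, clarify that exclusion on death ends follow-up without removing earlier data, and that revocation by nursing staff does not by itself erase a resident's data.

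The cost is one extra question at withdrawal, plus amended consent and data-protection wording with ethics notification. Limited consent is already accepted, so the principle is not new. Some deletions will remain, so the problem is reduced and made visible but not removed.
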